# Assessing the Efficacy of the ARMOR Tool–Based Deprescribing Intervention for Fall Risk Reduction in Older Patients Taking Fall Risk–Increasing Drugs (DeFRID Trial): Protocol for a Randomized Controlled Trial

**DOI:** 10.2196/55638

**Published:** 2024-06-11

**Keywords:** deprescribing, geriatric, fall risk–increasing drugs, FRIDs, ARMOR tool, Assess, Review, Minimize, Optimize, and Reassess, falls, older patients, fall risk

## Abstract

**Background:**

Falls in older patients can lead to serious health complications and increased health care costs. Fall risk–increasing drugs (FRIDs) are a group of drugs that may induce falls or increase the tendency to fall (ie, fall risk). 
Deprescribing is the process of withdrawal from an inappropriate medication, supervised by a health care professional, with the goal of managing polypharmacy and improving outcomes.

**Objective:**

This study aims to assess the effectiveness of a deprescribing intervention based on the Assess, Review, Minimize, Optimize, and Reassess (ARMOR) tool in reducing the risk of falls in older patients and evaluate the cost-effectiveness of deprescribing FRIDs.

**Methods:**

This is an open-label, parallel-group randomized controlled academic trial. Individuals aged 60-80 years who are currently taking 5 or more prescribed drugs, including at least 1 FRID, will be recruited. Demographic data, medical conditions, medication lists, orthostatic hypotension, and fall history details will be collected. Fall concern will be assessed using the Fall Efficacy Scale, and fall risk will be assessed by the Timed Up and Go test and Tinetti Performance-Oriented Mobility Assessment tool. In this study, all treating physicians will be randomized using a stratified randomization method based on seniority. Randomized physicians will do deprescribing with the ARMOR tool for patients on FRIDs. Participants will maintain diaries, and monthly phone follow-ups will be undertaken to monitor falls and adverse events. Physical assessments will be performed to evaluate fall risk every 3 months for a year. The rationality of prescription drugs will be evaluated using the World Health Organization’s core indicators.

**Results:**

The study received a grant from the Indian Council of Medical Research–Safe and Rational Use of Medicine in October 2023. The study is scheduled to commence in April 2024 and conclude by 2026. Efficacy will be measured by fall frequency and changes in fall risk scores. Cost-effectiveness analysis will also include the incremental cost-effectiveness ratio calculation. Adverse events related to deprescription will be recorded.

**Conclusions:**

This trial will provide essential insights into the efficacy of the ARMOR tool in reducing falls among the geriatric population who are taking FRIDs. Additionally, it will provide valuable information on the cost-effectiveness of deprescribing practices, offering significant implications for improving the well-being of older patients and optimizing health care resource allocation. The findings from this study will be pertinent for health care professionals, policy makers, and researchers focused on geriatric care and fall prevention strategies.

**Trial Registration:**

Clinical Trials Registry – India CTRI/2023/12/060516; https://ctri.nic.in/Clinicaltrials/pubview2.php

**International Registered Report Identifier (IRRID):**

PRR1-10.2196/55638

## Introduction

With the growing burden of multimorbidity among the older population, the concurrent use of multiple medications, known as polypharmacy, has become increasingly common. Unfortunately, polypharmacy is often associated with a high treatment burden and a diminished quality of life; more alarmingly, it can lead to the use of potentially inappropriate medications, increasing the risk of falls. Fall risk–increasing drugs (FRIDs) encompass a group of medications known to induce falls or elevate the risk of falling. These FRIDs include psychotropic drugs (eg, antipsychotics, antidepressants, benzodiazepines, and sedative-hypnotics), cardiovascular agents (eg, loop diuretics, digoxin, antihypertensives, and antiarrhythmics), and other agents (eg, hypoglycemic drugs, nonsteroidal anti-inflammatory drugs, opioids, anticholinergics, and antihistamines) [1-3]. Notably, falls are the leading cause of hospital admissions in the older population, with a reported prevalence of falls due to FRIDs reaching 41% [4].

In response to these challenges, deprescribing has emerged as a crucial strategy. Deprescribing is defined as “the process of identifying and discontinuing medications in which existing or potential harms outweigh potential benefits within the context of an individual patient’s care goals, function, values, and preferences” [5]. Various deprescribing strategies have been explored to reduce adverse events, including the STOPP/START criteria, Beer’s criteria, the Medication Appropriateness Index, and the ARMOR (Assess, Review, Minimize, Optimize, Reassess) tool [6,7].

This study is designed to evaluate the effectiveness of the ARMOR tool in reducing the fall risk in the geriatric population with FRID prescriptions as well as the cost-effectiveness of this intervention.

## Methods

### Study Design and Setting

This is a multicenter, open-label, parallel-group randomized controlled study. This non–drug intervention academic trial will
be conducted at selected sites after obtaining approval from all the respective Institutional Ethics Committees (IECs). The trial application has been submitted for registration with the Clinical Trial Registry – India, prospectively. The study duration is approximately 2 years, and the patient participation duration in the study is approximately 1 year**.**

### Participants

Participants will be enrolled in the study over a period of 1 year (approximately) based on the study’s eligibility criteria. Participants aged between 60 and 80 years; currently prescribed 5 or more medications, including at least one FRID; with a Montreal Cognitive Assessment (MoCA) score above 26; capable of walking 10 meters either independently or with the assistance of a walking aid (eg, walking stick, canes, or calipers); and voluntarily willing to participate and provide informed consent will be enrolled into the study.

Critically ill patients, patients with known neurological disorders (eg, cognitive impairment, dementia, Parkinsonism, or a history of stroke), older individuals receiving home care or specialized care, and older adults relying on a walker or wheelchair for mobility will be excluded from the study**.**

### Sampling Technique

This study will follow a proportionate-to-size sampling technique. Initially, the participants will be recruited from 4 major departments where FRIDs are most commonly prescribed. The departments will be sequentially numbered as 1, 2, 3, and 4 based on the proportion of older patients attending the department. The proportion of recruitment will be 50%, 20%, 15%, and 15% from departments 1, 2, 3, and 4, respectively. In the first round, the first department will be visited first for participant recruitment, and in the second round, the second department will be visited first, and so on for further rounds. Once the required number of participants is recruited from that outpatient department, that department will be removed from the sequential list. On the day of the visit to the respective department, eligible participants who are willing to participate in the study will be included, with 1 patient recruited per day.

### Randomization

#### Prescriber or Clinician randomization

After obtaining written informed consent, all treating physicians will be randomized using a stratified randomization method based on seniority in our study design. The clinicians will be divided into strata based on their seniority levels, for example, junior resident, senior residents, mid-level doctors (eg, assistant and associate professor levels), and senior doctors (eg, additional professor and professor cadre level). They will then randomly assign participants within each stratum to the intervention or control group. This stratified randomization ensures an equal distribution of doctors across the study groups, minimizing the potential for bias and contamination. Additionally, it accounts for any potential variations in expertise, experience, or treatment preferences among doctors of different seniority levels. The random allocation sequence will be generated using computer-generated random numbers. Enrolled participants will then be treated by the clinician randomized to the respective group.

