### Statistical Methods and Analysis

#### Sample Size

The sample size is estimated using the sample size formula for estimating proportion between two groups**.** Considering the reported fall incidence with FRIDs as 73% [12], the sample size is estimated to be 478 (each arm: 239), with 90% power (as the outcomes measures are only falls and do not include any mortality, we have set the power to 90%) and 5% level of significance to detect a minimum of 20% reduction in falls in the intervention group relative to the control group (relative risk reduction of 20%). Considering the dropout of 10%, the final sample size will be 526 (263 in each arm). A total of135 participants are expected to be recruited from each center.

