#### Data Analysis

The data will be entered in Research Electronic Data Capture (REDCap) and will be analyzed using Stata (version 16; StataCorp) software. Data will be stored in a secure server or cloud-based platform. A principal investigator and a co–principal investigator will have access to the REDcap data. The statistician will be given access to the blinded REDcap data. The occurrence of falls and fall risk during the study period will be summarized as frequency and percentages. The number of falls at these time points will be reported using the median (IQR) values. The fall risk score will be reported as mean (SD) or median (IQR) based on the normality of the data. The Mann-Whitney *U* test and Friedman test (chi-square test) will be used to analyze the change in the frequency of falls (%) at each time point between the groups and within the groups, respectively. The chi-square test will be used to analyze the fall risk score category at each time point between the groups. Additionally, repeated measures ANOVA (or Friedman test) and unpaired *t* test (or Mann-Whitney *U* test) will be used to assess the within-group fall risk score at different time points and at each time point within the group, respectively. Poisson regression analysis (both bivariate and multivariate) will be conducted to explore the association between the dependent variable (ie, the number of falls and fall risks assessed using Timed Up and Go and the Performance-Oriented Mobility Assessment) and independent factors (eg, age, gender, education, chronic illness, and intervention category). Adjusted risk ratios with 95% CIs will be reported for the factors included in the multivariate Poisson regression model. The rationality of prescriptions will be summarized using frequencies and percentages. Subgroup analysis will be performed for participants with recurrent fall history and different age categories.

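### Physicians carry the allocation, but the sample size and the named tests treat patients as independent: the 5% error rate is exceeded at any positive intracluster correlation, and 90% power holds only up to a design effect of about 1.08.

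*Protocol article*

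**What the plan says.** **Unit of randomisation.** Under Prescriber or Clinician randomization, the protocol article says that "all treating physicians will be randomized using a stratified randomization method based on seniority in our study design". The section closes with "Enrolled participants will then be treated by the clinician randomized to the respective group". The Methods paragraph of the abstract agrees: "Randomized physicians will do deprescribing with the ARMOR tool for patients on FRIDs".

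One sentence in the same section points elsewhere: "They will then randomly assign participants within each stratum to the intervention or control group". The Test Group and Control Group sections also speak of participants as having been randomised.

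**Sample size.** "The sample size is estimated using the sample size formula for estimating proportion between two groups". The inputs are a 73% fall incidence, a 20% relative reduction, 90% power and a 5% significance level. They give 478 patients (239 per arm), raised to 526 for 10% dropout. No other inflation appears.

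**Analysis.** Data Analysis names the Mann-Whitney, chi-square and unpaired t tests for comparisons at single time points. It adds a Poisson regression on "independent factors (eg, age, gender, education, chronic illness, and intervention category"). No physician term, random effect or cluster-robust variance is named.

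**The concern.** Patients of one physician share that physician's prescribing habits and case mix. The protocol recognises this itself: it justifies stratifying by seniority because doctors differ in expertise, experience and treatment preference. When arm is fixed at the level of the physician, this shared variation goes directly into the comparison between arms.

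Two things follow. Tests that assume independent patients use standard errors that are too small, so a difference between two sets of doctors can be read as an effect of deprescribing. And 478 patients carry less information than 478 independent ones, so the stated power may not be reached. The results are meant to inform prescriber workshops and policy, so a false positive would matter.

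**Working it through.** **Inputs from the Sample Size section:** control proportion 0.73; intervention proportion 0.73 × 0.80 = 0.584; difference 0.146; two-sided α = 0.05 (sidedness is not stated, but two-sided fits the stated number); 239 per arm.

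**Assumed inputs:** the number of physicians K (60, 40 or 24) and the ICC (0.01 or 0.05). The article gives neither.

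**Step 1. Reproduce the plan's figure.** With mean proportion 0.657, 2 × 0.657 × 0.343 = 0.4507, and 0.73 × 0.27 + 0.584 × 0.416 = 0.4400.

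n per arm = (1.96√0.4507 + 1.2816√0.4400)² / 0.146² = 220.1, so 221. With continuity correction it is 234, within 3% of the stated 239. Dropout: 478 × 1.10 = 526, as stated. The 239 is thus the size for an individually randomised trial, with no deliberate allowance for clustering.

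**Step 2. Power if patients were independent.**
Power(n) = Φ[(0.146√n − 1.96√0.4507) / √0.4400].
At n = 239: (2.257 − 1.316) / 0.663 = 1.419, which gives 92.2%.

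**Step 3. Room for clustering.** 90% power needs 221 independent patients per arm by this formula, so the largest tolerable design effect is 239/221 = 1.081. With DE = 1 + (m − 1) × ICC and m = 478/K, the limiting ICC is 0.081/(m − 1): about 0.012 for 60 physicians, 0.007 for 40 and 0.004 for 24.

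**Step 4. Power and error rate under assumed values.** Power is taken at 239/DE per arm. The type I error of a test that ignores clustering is 2[1 − Φ(1.96/√DE)].

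| Physicians | Patients each (m) | ICC | DE | Effective n per arm | Power | Type I error |
|---|---|---|---|---|---|---|
| 60 | 7.97 | 0.01 | 1.07 | 223 | 90.4% | 5.8% |
| 60 | 7.97 | 0.05 | 1.35 | 177 | 82.8% | 9.1% |
| 40 | 11.95 | 0.01 | 1.11 | 215 | 89.4% | 6.3% |
| 40 | 11.95 | 0.05 | 1.55 | 154 | 77.4% | 11.5% |
| 24 | 19.92 | 0.01 | 1.19 | 201 | 87.2% | 7.2% |
| 24 | 19.92 | 0.05 | 1.95 | 123 | 67.6% | 16.0% |

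These are large-sample approximations for the comparison of fall proportions on which the trial is sized. They assume equal cluster sizes and no small-sample correction. Unequal clusters, likely with recruitment split 50/20/15/15 across departments, and a small-sample correction would both lower power further.

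**The case against.** **The unit is not stated consistently.** This stands. One sentence can be read as assigning patients, and two later sections speak of randomised participants, so the text must be reconciled. It does not remove the problem. The section heading, its closing sentence and the abstract all point to the physician. Even if patients were assigned individually, they would then be treated by physicians belonging to one arm only, and outcomes would still be correlated within physician.

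**The power loss may be small.** This also stands in part. A reader might infer that the 90% power simply fails. The documents do not support that: 60 physicians with ICC 0.01 still give 90.4%, and the 68% figure needs the least favourable value of both assumed inputs. The article offers some hints on numbers: 526/135 suggests about four centres, and it names four departments and four example seniority levels. If every centre had all four departments with one physician per level in each (an assumption), there would be 4 × 4 × 4 = 64 physicians, giving power of 90.6% at ICC 0.01 and 83.5% at ICC 0.05. On that layout, 24 physicians would be only 1.5 per department per centre, which looks low.

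**The analysis plan could settle it.** The covariate list is introduced as examples, so other terms can be added, and a reader should not infer that leaving out centre or department is an error. Randomisation is stratified by seniority only, and extra fixed effects would strain a small number of clusters. But the article commits to a formula, a sample size, a power and named tests. A later document would have to contradict these, not complete them. A seniority covariate alone would not deal with correlation within physician.

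**A lower fall risk.** A reader might also set the 41% in the Introduction against the 73% and infer a further power failure. The 41% is not described as a one-year control-arm fall risk and may be a different quantity. It has no bearing on clustering and forms no part of this point.

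**Conclusion.** The concern holds in conditional form. The stated sample size and the named between-arm tests do not match a design in which physicians carry the allocation.

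The direction of the error-rate problem is certain for any positive ICC: an unadjusted comparison exceeds 5%, by little at the mild end (5.8%) and substantially at the severe end (16%) of the assumed range. The power loss depends on inputs that the article does not give. Across the same range, power runs from 90% to 68%, and it stays at 90% or above only while the design effect is no more than about 1.08.

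These sizes rest on the assumed physician numbers and ICCs, equal cluster sizes, and the plan's own 73% against 58.4%. The mismatch itself rests on the text alone.

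**What to change.** 1. State one unit of randomisation, and use it consistently in the abstract, the randomisation section and the two group descriptions.
2. Replace the unadjusted between-arm tests as the basis for inference with a mixed or GEE model (for example, modified Poisson) that has physician as the cluster, applies a small-sample correction, and adjusts for the seniority stratum used in randomisation. The simple tests can remain as description.
3. Restate power at 239/[1 + (m − 1) × ICC] per arm, using the actual number of participating physicians and an ICC range such as 0.01 to 0.05. Say that unequal cluster sizes lower it further.

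The cost is wording in the randomisation, sample size and analysis sections. No extra enrolment and no change to conduct or treatment is needed. The downside is wider confidence intervals and, quite possibly, a stated power below 90%.

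### Clinicians are randomized within seniority strata only, while patients are recruited by department quota at several centres, so arm balance by department and centre is left to chance

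*Protocol article*

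**What the plan says.** **Unit and strata.** Under Prescriber or Clinician randomization, "all treating physicians will be randomized using a stratified randomization method based on seniority". The strata are seniority grades, from junior resident to professor: "The clinicians will be divided into strata based on their seniority levels". Patients then follow the clinician: "Enrolled participants will then be treated by the clinician randomized to the respective group". The abstract's Methods paragraph also has physicians as the randomized unit.

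**Claimed benefit.** The same section states: "This stratified randomization ensures an equal distribution of doctors across the study groups, minimizing the potential for bias and contamination".

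**Recruitment.** Under Sampling Technique, "the participants will be recruited from 4 major departments where FRIDs are most commonly prescribed", and "The proportion of recruitment will be 50%, 20%, 15%, and 15% from departments 1, 2, 3, and 4, respectively". These quotas apply to departments, not to arms. Study Design and Setting says: "This is a multicenter, open-label, parallel-group randomized controlled study". The Sample Size section gives 135 as the number for which "participants are expected to be recruited from each center".

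**Analysis.** Data Analysis compares the arms by Mann-Whitney, chi-square and unpaired t tests, all unadjusted. Its Poisson model lists age, gender, education, chronic illness and intervention category as examples of factors. Department and centre are not among them.

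**Competing wording.** Prescriber or Clinician randomization also has a sentence about assigning participants at random within each stratum. Test Group and Control Group both describe participants as having been randomized.

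**The concern.** Seniority describes the doctor. Department and centre describe where the patients come from, and they are the units by which recruitment is organised. A scheme that balances the first leaves the second to chance, so the assurance that it minimizes bias does not extend to department or centre.

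If departments differ in underlying fall risk or in scope for deprescribing, an arm that happens to hold more clinicians from a high-risk department starts at a disadvantage that has nothing to do with the ARMOR tool. Unadjusted tests then count that difference as part of the treatment comparison, with a standard error that ignores it. Later adjustment helps only in part, because a department-centre with clinicians in one arm only offers no within-cell comparison.

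**Working it through.** **Inputs from the protocol article**
- Quotas 50/20/15/15% over four departments (Sampling Technique).
- 526 participants, 135 per centre (Sample Size). The number of centres is not stated; 526/135 = 3.9, so four are assumed.
- 73% fall incidence and a 20% relative reduction (Sample Size), giving 73% x 0.8 = 58.4%, a planned difference of 14.6 points. The stated 239 per arm is roughly reproduced (234 with continuity correction, two-sided 5%, 90% power). It does not bear on this point.
- Department 1 supplies 0.50 x 135 = 67.5 patients per centre.

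**Assumptions, not in the article**
- m participating clinicians per department per centre, with m = 2, 4, 6 or 8.
- Each is allocated 1:1, and clinicians share their department's patients equally.
- Department 1 differs in fall risk from the other three by 5, 10 or 20 points.

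**Step 1. One department at one centre wholly in one arm.** The chance is 2 x 0.5^m:
- m = 2: 50%
- m = 4: 2/16 = 12.5%
- m = 6: 3.1%
- m = 8: 0.8%

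The formula treats allocations as independent. With one clinician per seniority level (m = 4), each sits in a different stratum, so seniority stratification does not reduce the 12.5%.

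**Step 2. At least one such cell among 4 x 4 = 16.** 1 - (1 - 2 x 0.5^m)^16 gives about 100%, 88%, 40% and 12%. Simulated with allocation balanced within seniority and centre, it is about 100%, 84%, 28% and 6%.

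**Step 3. Effect on the comparison.** Simulation with 4 x 135 = 540 patients, no treatment effect, allocation balanced within seniority and centre, and an unadjusted two-proportion test at 1.96. The mean arm difference due to department is about zero. Each cell gives the 95th percentile of its absolute size, then the type I error:

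| Risk gap, department 1 | m = 2 | m = 4 | m = 6 | m = 8 |
|---|---|---|---|---|
| 5 points | 2.7 pts; 6.3% | 1.7; 6.0% | 1.2; 5.4% | 1.1; 5.4% |
| 10 points | 5.3 pts; 9.8% | 3.5; 7.7% | 2.4; 6.7% | 2.1; 5.3% |
| 20 points | 10.4 pts; 21.8% | 6.8; 14.5% | 5.5; 9.5% | 4.2; 8.2% |

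**Step 4. Check of the 10-point row by normal approximation.** The sampling standard error is sqrt(0.73 x 0.27 x 2/270) = 0.0382. The simulated SDs of the department-driven difference are 0.0248, 0.0170, 0.0129 and 0.0107. Type I error is 2 x [1 - Phi(1.96 / sqrt(1 + (SD/0.0382)^2))]. For m = 2 the argument is 1.96/1.192 = 1.644, giving 10.0%. The other three give 7.3%, 6.3% and 5.9%. Taking simulation and approximation together: about 10%, 7 to 8%, 6 to 7%, and 5 to 6%.

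**Step 5. Strata run across the whole trial instead of within centres.** The article does not say which applies. At a 10-point gap the simulated SDs are 0.022 (m = 2) and 0.015 (m = 4), with simulated type I error 8.3% and 5.6%. The Step 4 formula gives 8.9% and 6.8%. The inflation is somewhat smaller but in the same direction.

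**Step 6. With the remedy.** Balancing clinicians within department and centre (m = 2 or 4, 10-point gap) leaves no department in a single arm and makes the department-driven difference zero. Simulated type I error is 5.2% and 4.6%, the nominal level within simulation error.

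**The case against.** Several points on the other side have force.

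- **It is chance, not bias.** The expected imbalance over randomizations is zero. This stands. The harm lies in the one realised trial and in tests that treat the imbalance as absent.
- **A reader might infer that a whole department could land in one arm across the trial.** The documents do not support that. With four clinicians at each of four centres, the chance for department 1 is 2 x 0.5^16, about 0.003%. A one-arm department is realistic only within a single centre, and imbalances at different centres tend to offset.
- **A reader might infer that department fixes the drug class and the fall risk.** The article does not name the departments or give their fall rates. Its Introduction lists drug classes without tying them to departments. The risk gap is therefore an assumption.
- **The clinician count is unknown.** With eight or more per department per centre, the effect is small unless the risk gap is large.
- **Adjustment may follow.** The covariate list is illustrative, chronic illness may capture some case mix, and an unseen analysis plan may add factors. The missing model terms alone would therefore not be a finding. The point rests on the allocation, which is fixed at randomization, and on the assurance given for it.
- **Perhaps patients are randomized.** Some wording in the randomization, Test Group and Control Group sections reads that way, and the problem would then shrink. The abstract, the subsection's title and its closing sentence favour clinicians.
- **Mixed-arm departments invite contamination.** This is a real cost, but the present scheme already mixes the arms in 1 - 0.125 = 87.5% of department-centres with four clinicians.

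**Conclusion.** The point holds as one about uncontrolled chance imbalance. The allocation balances seniority and leaves unbalanced the two factors by which patients are recruited, so the stated assurance about bias is not supported for department or centre.

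The consequence ranges from negligible to material. At a 10-point gap, the department-driven difference (95th percentile) is 5.3 points with two clinicians per department per centre and 2.1 with eight, against a planned effect of 14.6. Type I error runs from about 10% down to 5 to 6%. At a 20-point gap with two clinicians it is about 22%.

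These figures rest on clinician randomization, four centres, equal patient load per clinician and an assumed risk gap. They do not show that the trial's result will be biased. The change is worth making because it is cheap and must precede randomization.

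**What to change.** Before the first clinician is randomized:

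1. Constrain or minimise the clinician allocation on centre and department, so that each department at each centre has clinicians in both arms where numbers allow. Keep seniority as a further balancing factor.
2. Include centre and department as factors in the between-arm model.
3. Reconcile the sentences that speak of randomizing participants with those that randomize clinicians.
4. Limit the statement about minimizing bias to what the scheme balances.

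Do not set department quotas per arm. In an open-label trial with known clinician arms, they would invite choosing patients by arm.

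The cost is a revised allocation list and two model factors; this change alone does not alter the sample size. Seniority will be balanced less tightly where clinicians are few. Departments will as a rule hold both arms, so contamination within departments may rise slightly.

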#### Blinding (Masking)

Considering the nature of the intervention proposed, this study is designed as an open-label study; the participants and the intervention implementing team will not be blinded to the intervention. However, the statistician performing data analyses will be blinded to group assignments.

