### Test Group

Participants randomized to this group will be managed using the ARMOR tool–based deprescribing intervention, which contains 5 steps—Assess, Review, Minimize, Optimize, and Reassess. A clinical pharmacologist provides a summary report of steps 1 and 2 of the ARMOR tool to the treating physician. The treating physician will complete steps 3 to 5.

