### Control Group

Participants randomized to the usual care group will receive treatment as per the standard practice or protocol. As there are no established gold standards for effective, deprescribing interventions, usual care is chosen as a comparator.

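### The article gives two different units of randomisation; if physicians are the unit, the recruitment steps it describes leave room for patient selection after allocation

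*Protocol article*

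**What the plan says.** Under Prescriber or Clinician randomization the article states that "all treating physicians will be randomized using a stratified randomization method based on seniority in our study design". Two sentences later it says: "They will then randomly assign participants within each stratum to the intervention or control group". The paragraph closes with: "Enrolled participants will then be treated by the clinician randomized to the respective group". It also credits the seniority strata with limiting bias and contamination. The Methods part of the abstract agrees with physician randomisation, since it has randomised physicians doing the deprescribing.

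The arm descriptions read differently. Test Group: "Participants randomized to this group will be managed using the ARMOR tool–based deprescribing intervention". Control Group: "Participants randomized to the usual care group will receive treatment as per the standard practice or protocol".

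On recruitment, Sampling Technique says that on the day a department is visited "eligible participants who are willing to participate in the study will be included, with 1 patient recruited per day". It does not say which patient is taken when several qualify. On masking, Blinding (Masking) says "the participants and the intervention implementing team will not be blinded to the intervention", and the statistician is the only role named as blinded.

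**The concern.** A trial that randomises doctors and one that randomises patients need different safeguards at entry. When patients are randomised after consent with concealment, nobody can steer a given patient into an arm. When doctors are randomised first, the arm belongs to the doctor. Anyone who chooses which patient to approach, or which doctor that patient sees, may then be able to tell which arm the patient will join.

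If frailer or less willing patients enter the two arms unequally, the arms differ in fall risk before any deprescribing takes place. Such a difference can look like a treatment effect or hide one, and covariate adjustment at analysis repairs it only in part. The seniority strata do not address this: they balance the doctors, not the patients enrolled under them.

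**Working it through.** **1. Unit of allocation, side by side**

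| Place in the article | Unit stated or implied |
|---|---|
| Abstract, Methods | Physician |
| Prescriber or Clinician randomization: heading, first and last sentences | Physician |
| Same section, sentence on assignment within strata | Participant |
| Test Group | Participant |
| Control Group | Participant |

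The strata are defined by clinicians' seniority, so assigning participants within them has no clear meaning unless each participant is already tied to a clinician.

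**2. Sequence under the physician reading**

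The clinician is randomised and the enrolled patient is then treated by that clinician. Enrolment runs for about 1 year (Participants), one patient per visit day. The article states no order for choosing among eligible patients and no rule for routing a patient to a particular clinician. The route for selection is therefore open. Nothing in the text shows that it is used.

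**3. The plan's own figure**

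Inputs from Sample Size: control risk 0.73, relative reduction 20%, so test risk 0.73 × 0.8 = 0.584 and difference 0.146; 5% level (taken as two-sided); 90% power.

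n = [1.96·√(2·p̄(1−p̄)) + 1.2816·√(p₁(1−p₁) + p₂(1−p₂))]² / d², with p̄ = 0.657

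= [1.96·√0.4507 + 1.2816·√0.4400]² / 0.0213 = 221 per arm, or 234 with continuity correction.

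The stated 239 is close to the corrected value. It comes out exactly, without correction, if the test risk is taken as 0.59. Dropout: 478 × 1.1 = 526, or 263 per arm, as stated.

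**4. Illustration of what a case-mix gap would do**

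Assumptions: no true treatment effect, control risk 0.73, test-arm risk 0.73 − b from case mix alone, 239 per arm, independent patients, two-sided 5% z-test. The values of b are assumed because the documents give none.

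se₀ = √(2·p̄(1−p̄)/n); se₁ = √([p₁(1−p₁) + p₂(1−p₂)]/n)

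P(significant) = Φ((b − 1.96·se₀)/se₁) + Φ((−b − 1.96·se₀)/se₁)

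- b = 0.03: se₀ = 0.0413, se₁ = 0.0413; 0.1086 + 0.0036 = 0.112.
- b = 0.05: se₀ = 0.0417, se₁ = 0.0417; 0.2229 + 0.0008 = 0.224 (0.241 at 263 per arm).

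| b (percentage points) | 2 | 3 | 5 | 8 | 10 |
|---|---|---|---|---|---|
| P(significant), 239 per arm | 7.8% | 11.2% | 22.4% | 47.2% | 65.0% |

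One way a 3-point gap could arise, again assumed: two risk classes with 88% and 58% fall risk. If half of control patients are in the high-risk class, the arm's risk is 0.5 × 0.88 + 0.5 × 0.58 = 0.73. If 40% of test patients are, it is 0.4 × 0.88 + 0.6 × 0.58 = 0.70.

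**The case against.** The physician reading is the better supported one, and the participant wording may be loose: participants within strata could mean clinicians, and the arm descriptions could be shorthand for the arm a patient ends up in. That would make the contradiction an editing matter. It would still have to be edited, because a reader cannot tell which design is meant.

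The stronger objection concerns selection. A reader might infer that unmasked staff pick patients already knowing the arm, and that the arm is known at consent and when the nurse scores baseline. The article does not say this. It does not identify the recruiters; the masking text covers participants and the implementing team. Recruitment is by department rather than by physician, and enrolment is mentioned before treatment by the allocated clinician, so a patient's arm may stay open until routing. The paragraph opens with written informed consent without making clear whose. The article also condenses a full protocol, which may fix the picking rule and the concealment. All of this stands, and it makes the selection point a conditional one.

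It is also fair that the gaps of 3 and 5 points are not evidence from this trial, and that the calculation treats patients as independent although bias of this kind arises when physicians are the unit. With clustering by physician, a simple two-proportion test would not in general hold 5% anyway.

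Finally, a reader might go on to ask that the monthly caller be masked. The Follow-Up Phase section gives those calls a role in adherence to the intervention, so that request conflicts with the plan and is not made here.

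**Conclusion.** The contradiction on the unit of allocation is in the text, needs no inference, and must be resolved. The selection risk holds conditionally: if physicians are the unit, the steps as described leave room for whoever recruits to know or influence a patient's arm, and the seniority strata do not close that gap. If participants are individually randomised after consent with concealment, the risk largely disappears, but the physician-randomisation text is then wrong.

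The documents support no statement that recruiters know the arm, that bias will occur, or which way it would run. The figures of about 11% and 22% show only how sensitive a comparison of this size is to assumed case-mix gaps of 3 and 5 points, which are small beside the planned 14.6-point effect. They are not estimates of this trial's error rate.

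**What to change.** 1. State one unit of allocation, and make the abstract, the Randomization section, Test Group and Control Group agree with it.
2. On each recruitment day, take the first eligible and willing patient in the department's registration order.
3. Complete consent, eligibility and the full baseline (fall history, Timed Up and Go, Performance-Oriented Mobility Assessment), and lock them in REDCap before the arm or the clinician is disclosed.
4. Then route the patient to a clinician from a concealed, pre-generated list, not by staff choice.
5. Where feasible, have the existing nurse score the follow-up Timed Up and Go and Performance-Oriented Mobility Assessment without being told the arm. Leave the monthly call as planned.

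The cost is a wording change, a reordering of existing steps, a routing list to prepare, and a little less flexibility on recruitment days. The sample size does not change.
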